#### **Safety analysis:**

The frequency of adverse events and serious adverse events and the relationship to the study drug will be analyzed descriptively guided by MedDRA classification. Gender- as well as age-specific aspects will be given consideration by means of additional analyses if considered appropriate.

**Confidential**

### 13.2 Interim Analysis

A fixed sample design is planned without confirmatory statistical testing for early decision making. There is no pre-planned efficacy interim analysis.

### 13.3 Sample Size Calculation

The sample size was calculated on the basis of the primary hypothesis, using own preliminary case series data (n=13 patients; [10]) and a similar placebo-controlled trial (N=20 patients; [31]) evaluating the efficacy of varenicline on the improvement in SARA total score in patients with SCA3.

Hence, assuming a minimum clinically relevant improvement in the SARA total score of 1.5 points [28] (the absolute change under verum is by 1.5 score points better as the change under placebo) and a standard deviation of the individual SARA change of 3.0 (which results in a standard deviation of 4.2 assuming an intra-patient correlation of 0.6), a **sample size of 86** (85 is calculated but 2 sequences are needed) **in total** is needed to have 90% power to detect a difference in means of 1.5, using a paired t-test with a 0.05 two-sided significance level [Software used: nQuery Advisor 7.0].

Assuming a dropout rate of about 20%, **a total of 108 patients have to be allocated to the trial**. With a proportion of about 50-55% recruited patients out of the number to be screened, 200 patients have to be assessed for eligibility.

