## 7.4 Number of patients

To be randomized: n = 108 patients

To be analyzed: n = 86 patients (expected to complete both phases)

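### Section 13.3: an SD of change of 3.0 with a correlation of 0.6 between the period changes gives 2.68 for the paired difference, not 4.2; the stated 4.2 is the value for uncorrelated changes, and 86, 108 and 90% power follow from it alone

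*Protocol*

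**What the plan says.** Protocol section 13.3 sizes the trial on the primary endpoint, the change in SARA total score from each period's own baseline (section 6.2). The target difference is 1.5 points, explained as "the absolute change under verum is by 1.5 score points better as the change under placebo". The variability is given as a "standard deviation of the individual SARA change of 3.0 (which results in a standard deviation of 4.2 assuming an intra-patient correlation of 0.6".

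The test and power are stated as "is needed to have 90% power to detect a difference in means of 1.5", "using a paired t-test with a 0.05 two-sided significance level". The section reports 85 as the calculated number, raised to 86 so that it divides over two sequences, and 108 allocated after a dropout rate of about 20%. Section 7.4 repeats the result: "To be analyzed: n = 86 patients (expected to complete both phases". The synopsis gives the same 86 and 108.

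**The concern.** In a crossover analysed by a paired t-test, a positive correlation between a patient's two period results makes the SD of their difference smaller than it would be at zero correlation. Section 13.3 names a correlation of 0.6 and gives it as an assumption behind the move from 3.0 to 4.2. But 4.2 is what one gets, to rounding, with no correlation at all, so the result does not follow from the inputs said to produce it.

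This sentence is the only derivation of the 86 and 108. The design is fixed, with no efficacy interim analysis (sections 7.1 and 13.2), so the number of patients exposed is settled here. As written, a reader cannot tell whether the trial is planned at 90% power for 1.5 points or is well over twice the size its stated assumptions require.

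**Working it through.** **Inputs, all from section 13.3:** difference 1.5; SD of the individual change 3.0; correlation 0.6; SD used 4.2; two-sided 5%; power 90%; paired t-test; dropout 20%.

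**Step 1. Reproduce the plan's figure from 4.2.** Power of the paired t-test comes from the noncentral t distribution with n - 1 degrees of freedom and noncentrality (1.5/SD) x sqrt(n).

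- SD 4.2: the smallest n with at least 90% power is 85 (90.2%). At n = 86 power is 90.6%. The normal approximation gives 82.4.
- Dropout: 86/0.8 = 107.5, rounded up to 108.

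So 85, 86, 108 and 90% all follow from 4.2.

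**Step 2. Check how 4.2 was reached.** For two changes with common SD s and correlation rho between them, the SD of their difference is s x sqrt(2(1 - rho)).

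- rho = 0.6: 3.0 x sqrt(0.8) = 2.68
- rho = 0: 3.0 x sqrt(2) = 4.24
- Solving for rho at 4.2: 1 - 4.2²/(2 x 3.0²) = 1 - 17.64/18 = 0.02. If 4.2 was rounded from anywhere between 4.15 and 4.25, rho lies between 0.04 and -0.003.
- Keeping both 4.2 and rho = 0.6 would need an SD of the individual change of 4.2/sqrt(0.8) = 4.70, not 3.0.

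**Step 3. Sample size and power under each SD.**

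| SD of the paired difference | How obtained | n for 90% power | Power at 86 |
|---|---|---|---|
| 4.20 | as stated | 85 | 90.6% |
| 4.24 | 3.0 x sqrt(2), rho = 0 | 87 | 90.0% |
| 2.68 | 3.0 x sqrt(0.8), rho = 0.6 | 36 | 99.9% |

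With the unrounded 4.24 the exact search returns 87 only because power at 86 falls just short of 90% before rounding. With 2.68, 36 completers become 36/0.8 = 45 after dropout, and 86 completers have 90% power for a difference of 0.95 points. The planned 86 is then 86/36 = 2.4 times the number needed.

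**Step 4. Look for a reading under which 3.0, 0.6 and 4.2 agree.** Each patient contributes four SARA scores: a baseline and an end-of-period score in each period. Suppose any two of them correlate at 0.6 with a common score SD.

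- For a change SD of 3.0, the score SD must be 3.0/sqrt(0.8) = 3.354.
- The covariance of the two changes is score variance x (0.6 - 0.6 - 0.6 + 0.6) = 0.
- The SD of the difference between changes is therefore 3.0 x sqrt(2) = 4.24.

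The three numbers agree here. But once 3.0 is given, the result is 4.24 for any common score correlation, so 0.6 has no role in the step to which the sentence attaches it.

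Other readings do not reach 4.2. Taking 3.0 as the SD of a single score, with 0.6 within a period and independent changes, gives 2.68 x sqrt(2) = 3.79 and n = 70. Taking 3.0 as already the SD of the paired difference gives n = 44.

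**The case against.** The strongest defence is that the protocol speaks of an intra-patient correlation and does not say between which quantities. With a separate baseline in each period, an equal correlation of 0.6 among all four scores makes the period changes uncorrelated, and 4.2 is then right. This stands. A reader might infer from the mismatch that no interpretation yields 4.2; step 4 shows that one does. It does not rescue the sentence, which never states that structure and presents 4.2 as resulting from 3.0 under a correlation of 0.6. The SDs reported for the case series in section 5.1 (7.1 and 6.8) are well above the score SD of 3.354 this reading needs. However, that questions the 3.0 rather than the step to 4.2, and section 13.3 also draws on another trial whose data are not in the protocol.

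A second objection is that 86 patients and 90% power do fit together. That is also correct: both follow from 4.2. The fault is confined to the step from 3.0 to 4.2.

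Third, the practical harm is limited. The analysis model, significance level, endpoint and enrolment are untouched. A reader might also worry that a blinded re-estimation of the SD would use the wrong benchmark, but the protocol plans no such check.

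Finally, rewriting the section with 2.68 and power above 99% would introduce an error if the period changes are in fact uncorrelated. This is accepted, and the fix makes that option conditional.

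**Conclusion.** The concern holds for the derivation of the SD. As the sentence reads, with 0.6 applied between the two period changes, 3.0 leads to 2.68, while the stated 4.2 corresponds to a correlation of about zero. The distance is large: 36 against 85 completers for 90% power, or 99.9% against 90.6% power at 86.

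A reader might conclude that the trial is underpowered. The documents do not support this. If 3.0 and 0.6 are both right for the period changes, the error is conservative. If the changes are uncorrelated, 86 completers give 90.0% power with the unrounded 4.24 and 90.6% with 4.2, as planned.

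These figures rest on the protocol's own difference of 1.5, its SD of change of 3.0 and its paired t-test. Whether 3.0 or 0.6 is realistic cannot be judged from the protocol, nor does it show which of 3.0, 0.6 and 4.2 carries the intended meaning.

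**What to change.** Correct the one sentence in section 13.3. Remove 0.6 from the step between 3.0 and 4.2, and state that the changes in the two periods are assumed uncorrelated, so that the SD of the paired difference is 3.0 x sqrt(2) = 4.24, about 4.2. The 86, the 108 and the 90% power then stay. If 0.6 was meant as the correlation between single SARA scores, it can be mentioned separately as such.

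Only if the sponsor confirms that 0.6 is the correlation between the two period changes should the section give an SD of 2.68 and the resulting power of 86 completers (99.9% for 1.5 points). It would then help to add a line saying why 86 is kept when 36 would meet the 90% target.

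The cost is one corrected sentence, plus that line if the second option applies. No change to enrolment, design or analysis is needed.

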### 13.4 Populations included in the Analysis

The primary endpoint of the clinical subject will be analysed primarily according to the intention-to-treat (ITT) principle. Amongst others, this means that, whenever possible, the subjects will be analysed according to the treatment sequence to which they were randomised, irrespective of whether they refused or discontinued the treatment or whether other protocol violations are revealed.

An analysis per-protocol (PP) for a specific endpoint excluded or censored endpoint information considering major protocol deviations potentially effecting subjects' specific endpoint value, e.g. in the case of major violation of eligibility criteria, lack of sufficient treatment per protocol, major use of prohibited concomitant therapy, or unsatisfactory examinations or evaluations for endpoint assessment. Exclusions or censoring with respect to endpoints confirmatory analysed after unblinding of the statistician will be listed and accounted for (e.g. incidentally finding of major violation of eligibility criteria during secondary analyses). The PP analyses will be performed for the purpose of a sensitivity analysis and investigating robustness of results.

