## 9.9 Blinding and Emergency Codes

The trial will be subject and investigator blinded. Study personnel involved in patient recruitment and trial activities will have no access to the randomization list provided by the IBE. The statistician responsible for the final analysis will also have no access to the list.

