### **Regular unblinding:**

As a matter of principle, unblinding happens regularly when the trial database is closed, after blinded data review following resolution of queries.

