## 13 Statistical Methods

### 13.1 Planned Statistical Analyses

#### **Analysis of primary endpoint:**

For the primary outcome change in SARA total score (DeltaSARA), the null hypothesis will be tested that the mean change is the same on placebo and on acetyl-DL-leucine. The significance level alpha is set to 5%.

The primary efficacy analysis will be performed according to the intention-to-treat (ITT) principle. Absolute change calculated as the difference between the period-level baseline score and the score measured at the 2-week visit and at the 6-week visit of the verum/ placebo period will be considered for a model-based primary efficacy analysis. If not revised in the *statistical analysis plan* (SAP), a linear mixed effects model for DeltaSARA will be performed (fixed effects: factors for treatment and visit, treatment-by-visit interaction, mean of both period-level baseline SARA total scores as covariate; normally distributed patient-specific random intercepts) in order to deal with repeated measurements within periods and measurements not made at equivalent times on each subject (due to unscheduled or missed clinic visits). This subject-specific modelling approach allows individual change scores over time to be calculated. To analyse the differences between both treatments at the end of the 6-week treatment period, 95% confidence intervals will be provided to quantitatively describe treatment effects.

Sensitivity analyses will be performed on a per protocol approach which accounts for compliance with medication according to the protocol. Additional efficacy analyses adjusting for genetically vs. sporadic CA, gender, age, or trial site, will be performed. Besides, the robustness of the overall result will be investigated by sensitivity analyses adjusting for speech-/physiotherapy (as considered appropriate during the blinded data review depending on the data quality). Further methodological details will be provided in the SAP.

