**Confidential**

- the intake of concomitant medications not permitted during the trial
- missed evaluations
- non-compliance with the IMP (e.g. intake of trial drug < 1.5 g daily during treatment period (week 3-6), depending on the duration of intake per treatment period and drug counting)
- any non-adherence to the protocol that would have an impact to the subject's rights, safety or welfare.

Minor protocol deviations may include, but are not limited to, e.g.:

- intake of trial drug < 5 g daily and > 1.5 g daily during the treatment period (week 3-6), depending on the duration of intake per treatment period
- unscheduled visits

After a subject has been enrolled, it is the investigator's responsibility to make a reasonable effort to correct any protocol violations and to continue the subject's participation in the trial. Protocol violations do not justify withdrawal of a subject from the trial.

Protocol violations will be reported to the sponsor/sponsor delegated person during the course of the trial in the monitoring reports.

Protocol violations will be listed and the impact on the evaluation of the subjects concerned will be discussed and evaluated at regular time intervals (depending on the amount of protocol violations), and prior to unblinding for a statistical analysis. Handling of major deviations in statistical analyses will be fixed during a blinded data review before unblinding.

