### **14.3.2 Case Report Form (CRF)**

CRFs provided by the sponsor will be used to document the subject's data during the course of the trial. The data will be pseudonymized, processed and stored according to local law. This also allows preservation for future use.

The investigator has ultimate responsibility for the accuracy, authenticity, timely collection and reporting of all clinical, safety, laboratory data entered on the CRFs. All these data may only be entered and updated in the CRFs by authorized trial personnel.

In case of paper CRFs the completed pages will be sent to the data management for data entry and will be transferred to the sponsor delegated person at the end of the trial. A copy of each CRF page is archived at the investigator's site. The CRFs must be signed by the investigator or by an authorized staff member (physician) to confirm the correctness of the data documented on the CRF. Any corrections to entries made in the CRFs, source documents must be dated, signed and explained (if necessary) and should not obscure the original entry.

Changes are recorded (audit trail) and have to be annotated, once the respective CRF has been marked as completed.

After data cleaning (see section 14.1) and blinded data review, the data base will be locked and be used for unblinded statistical analysis.

Copies of the completed query forms will be stored per subject together with the CRF at the trial site.

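### Section 13.4 lets per-protocol exclusions and censoring be made after the statistician is unblinded, in tension with the blinded-review rule in 13.5; only this sensitivity analysis is exposed

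*Protocol*

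**What the plan says.** Three places in the protocol set one order of events.

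- Section 13.5 (Protocol Violations): "Handling of major deviations in statistical analyses will be fixed during a blinded data review before unblinding".
- Section 9.10 (Regular unblinding): "unblinding happens regularly when the trial database is closed, after blinded data review following resolution of queries".
- Section 14.3.2 (Case Report Form): "After data cleaning (see section 14.1) and blinded data review, the data base will be locked and be used for unblinded statistical analysis".

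Section 13.4 defines the per-protocol analysis by excluding or censoring endpoint information affected by major deviations. It then adds: "Exclusions or censoring with respect to endpoints confirmatory analysed after unblinding of the statistician will be listed and accounted for". The example given in brackets is "incidentally finding of major violation of eligibility criteria during secondary analyses". The paragraph closes with the purpose of the analysis: "The PP analyses will be performed for the purpose of a sensitivity analysis and investigating robustness of results".

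For the main test, section 13.1 states: "The primary efficacy analysis will be performed according to the intention-to-treat (ITT) principle".

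**The concern.** A per-protocol analysis supports an intention-to-treat result only if its membership was settled without knowledge of allocation and outcome. The sentence in 13.4 allows for membership, or single endpoint values, to change after that knowledge exists. It names confirmatory endpoints in general, so it covers the change in SARA total score and, if the primary test succeeds, EQ-5D-5L as well (section 13.1).

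At stake is how much agreement between the two analyses can show. If someone who can see the results decides which late-found cases count as major, agreement is weaker evidence of robustness, and disagreement is harder to interpret. Listing the exclusions lets a reader see that they happened. It does not restore the comparison that blinded decisions would have given.

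**Working it through.** **1. Order of events.** Sections 9.10, 13.5 and 14.3.2 agree: query resolution and blinded review, then database lock, then unblinding and analysis. The handling of deviations is complete before unblinding. Section 13.4 adds a further point, after unblinding, at which exclusions or censoring can still occur.

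**2. Reading of the 13.4 sentence.** Its grammar is loose. The words about unblinding could describe when the endpoints are analysed, or when the exclusions are made. The bracketed example decides it: a violation discovered during secondary analyses is discovered after unblinding, so the sentence is about late exclusions.

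**3. Conditions attached.** The sentence requires listing and accounting. It does not require a pre-fixed rule, a blinded decision-maker, or a parallel report of the set as it stood at the blinded review.

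**4. What is exposed.** The primary analysis is intention-to-treat (13.1, 13.4) and uses all observed data (13.6). Section 13.4 keeps patients in it whatever protocol violations come to light. The per-protocol clause therefore cannot alter the confirmatory test.

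**5. Planning figures.** Inputs from section 13.3: difference 1.5, SD of the paired difference 4.2 as stated, two-sided alpha 0.05, power 90%, dropout about 20%.

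- Normal approximation: n = ((1.960 + 1.282) × 4.2 / 1.5)² = 82.4.
- Exact noncentral t: n = 85, as the protocol states; power at 86 is 90.6%.
- Dropout: 86 / 0.80 = 107.5, rounded up to 108, as stated.
- Standard error: 4.2 / √86 = 0.453 points.

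None of these figures changes under this point.

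**6. Illustration of the worst case.** Assume no treatment effect and 86 paired differences drawn from a normal distribution with mean 0 and SD 4.2. Remove the k patients with the least favourable differences, then apply a paired t-test at two-sided 5%. Two simulations (20,000 and 40,000 runs) agree closely.

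| k removed | Mean shift towards verum (points) | In standard errors | Nominally significant in favour of verum |
|---|---|---|---|
| 0 | 0 | 0 | 2.5% |
| 1 | 0.121 | 0.27 | 4.9% |
| 2 | 0.227 | 0.50 | 8.2% |
| 3 | 0.325 | 0.72 | 12.4% to 12.6% |
| 4 | 0.417 | 0.92 | 17.7% to 17.8% |

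Limits of the table: 86 is the number expected to complete both periods, not a per-protocol set. The planned model is a mixed model, not a paired t-test. Patients are removed purely on outcome, whereas 13.4 covers only patients with a major deviation. If late exclusions are unrelated to outcome, the bias is zero. The percentages do not depend on the SD; the shifts in points are proportional to it.

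**The case against.** The strongest reply is that the two sections address different things. Section 13.5 fixes the handling of deviations, while 13.4 deals with a case discovered later. A rule agreed under blinding can be applied to a late case without conflict. That reading is possible, and it is why the passages are in tension rather than flatly incompatible. But the protocol does not state it.

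The clause also imposes a duty to disclose, and its one example is an eligibility violation. That concerns status at entry and leaves less room for outcome-driven judgement than a compliance decision would. Both points stand as partial mitigation. The softer terms in 13.4, about sufficiency of treatment, extent of prohibited therapy and quality of examinations, belong to its general per-protocol definition and are not tied to the late-exclusion clause. Section 13.5 does not use them and gives a numerical example for non-compliance.

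Section 9.9 says of the randomization list: "The statistician responsible for the final analysis will also have no access to the list". This does not close the gap, because 13.4 itself presupposes that the statistician has been unblinded, and 14.3.2 describes the analysis as unblinded.

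Per protocol is also only one check. Section 13.1 adds covariate-adjusted analyses, the synopsis adds multiple imputation, and section 13.6 adds scenarios of informative missingness. This stands and limits the consequence.

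Finally, the detail could be left to the SAP, which is not at hand and may settle it. The point is not that detail is missing, however. The protocol contains a sentence that allows late changes, and that sentence needs correcting wherever the detail is placed.

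A reader might infer from the table that the trial's false-positive rate rises to 17.8%. The documents do not support that: the confirmatory test is intention-to-treat, and the table describes deliberate outcome-based selection in a non-confirmatory analysis. Nor does 13.4 give open permission to redefine the set at will.

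**Conclusion.** The point holds as a minor to moderate weakness in one sensitivity analysis. Section 13.4 permits per-protocol data to change with allocation and outcomes visible, and nothing in the protocol ties such changes to the decisions made at the blinded review. The confirmatory result, its alpha and the sample size are unaffected.

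The likely size cannot be derived from the protocol, because it depends on how many violations are found late and whether removing them is related to outcome. It runs from no bias up to the illustrative shifts in the table, which are a ceiling for a given number of removals under the stated assumptions, not a forecast. The conclusion rests on reading the 13.4 sentence as its own example suggests, and on the protocol text alone.

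**What to change.** Replace the sentence in 13.4 with wording to this effect: the per-protocol set and all censoring of endpoint data are fixed at the blinded data review and form the per-protocol analysis of record; deviations found after unblinding are listed in the report and do not change that set or its data; any analysis that removes them is shown alongside and labelled post hoc.

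This brings 13.4 into line with 9.10, 13.5 and 14.3.2. The cost is a short edit to the protocol and the same wording in the SAP. The downside is small: a genuine violation found late stays in the per-protocol set of record, but its effect is still shown in the post-hoc run.
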